# T-tube drainage versus choledochojejunostomy in hepatolithiasis patients with sphincter of Oddi laxity: study protocol for a randomized controlled trial

**DOI:** 10.1186/s13063-020-04483-z

**Published:** 2020-06-29

**Keywords:** Hepatolithiasis, Sphincter of Oddi, Choledochojejunostomy, T-tube drainage

## Abstract

**Background:**

Residual and recurrent stones remain one of the most important challenges of hepatolithiasis and are reported in 20 to 50% of patients treated for this condition. To date, the two most common surgical procedures performed for hepatolithiasis are choledochojejunostomy and T-tube drainage for biliary drainage. The goal of the present study was to evaluate the therapeutic safety and perioperative and long-term outcomes of choledochojejunostomy versus T-tube drainage for hepatolithiasis patients with sphincter of Oddi laxity (SOL).

**Methods/design:**

In total, 210 patients who met the following eligibility criteria were included and were randomized to the choledochojejunostomy arm or T-tube drainage arm in a 1:1 ratio: (1) diagnosed with hepatolithiasis with SOL during surgery; (2) underwent foci removal, stone extraction and stricture correction during the operation; (3) provided written informed consent; (4) was willing to complete a 3-year follow-up; and (5) aged between 18 and 70 years. The primary efficacy endpoint of the trial will be the incidence of biliary complications (stone recurrence, biliary stricture, cholangitis) during the 3 years after surgery. The secondary outcomes will be the surgical, perioperative and long-term follow-up outcomes.

**Discussion:**

This is a prospective, single-centre and randomized controlled two-group parallel trial designed to demonstrate which drainage method (Roux-en-Y hepaticojejunostomy or T-tube drainage) can better reduce biliary complications (stone recurrence, biliary stricture, cholangitis) in hepatolithiasis patients with SOL.

**Trial registration:**

Clinical Trials.gov: NCT04218669. Registered on 6 January 2020.

## Background

Hepatolithiasis (HL), defined as the occurrence of stones in any intrahepatic bile duct proximal to the confluence of the right and left hepatic ducts, is a common disease in Southeast Asia and accounts for up to 20% of all cases of gallstone disease. Although rare in Western countries, with a reported incidence of 0.6 to 1.3%, an increasing trend has been observed due to immigration from endemic areas and the westernization of diets [1]. HL is benign in nature, but without appropriate treatment, it can lead to repeated cholangitis, liver abscesses, biliary strictures, secondary biliary cirrhosis and even cholangiocarcinoma [2].

The principles of HL management are clearance of stones, correction of strictures, removal of non-functioning liver segments that harbour bacteria and serve as foci of infection, and restoration of bile drainage [3]. The curative management of HL is difficult since the pathogenesis of this condition is not completely understood, and the best definitive management of HL is a multidisciplinary approach that consists of laparoscopic, open, endoscopic and percutaneous surgical approaches. However, residual and recurrent stones remain one of the most important challenges of HL and are reported in 20 to 50% of patients treated with these therapies. The risk factors associated with stone recurrence were reported to be liver atrophy, bile duct stricture, dilatation, residual stones and sphincter of Oddi laxity (SOL) [4, 5].

SOL results in the reflux of duodenal fluid and enteric bacterial infections, which lead to the formation of stones in the biliary tract. Roux-en-Y hepaticojejunostomy (HJ) shows considerable advantage in preventing the reflux of intestinal contents into the bile duct [6, 7]. There is no consensus on which drainage method is better for HL patients with SOL, and there are no prospective randomized controlled studies that have evaluated the effects of different drainage methods. As a result, we decided to carry out a randomized controlled trial (RCT) to evaluate the therapeutic safety and perioperative and long-term outcomes of HJ versus T-tube drainage for HL with SOL.

## Methods/design

### Study design

This prospective, single-centre, randomized and interventional clinical trial is being conducted at the First Affiliated Hospital of Anhui Medical University, which began in February 2020 and is expected to end in 2026. Patients with diagnosed HL who meet the entry criteria will be recruited and randomly assigned to undergo either T-tube drainage or Roux-en-Y HJ. The flowchart according to the Consolidated Standards of Reporting Trials (CONSORT) statement is shown in Fig. 1, and the schedule of enrolment, interventions and assessments are summarized in Fig. 2. The Standard Protocol Items: Recommendations for Interventional Trials (SPIRIT) guidelines are provided in Additional file 1. The full protocol and the datasets analysed during the current study are available on request from the corresponding author.

**Fig 1 Fig1:**
[figure not shown]
Flowchart according to CONSORT

**Fig 2 Fig2:**
[figure not shown]
Schedule of enrollments, interventions and assessments. Abbreviations: t_1_, 3 months after surgery; t_2_, 6 months after surgery; t_3_, 1 year after surgery; t_4_, 2 years after surgery; t_5_, 3 years after surgery

### Number of patients needed

The sample size is based on a two-sided *t* test for differences with respect to the primary parameter and the primary analysis. In a retrospective analysis of our own series, the incidence of biliary complications was 30% in patients with HL with SOL undergoing T-tube drainage. The calculated sample size was 186 (93 per group), with 80% statistical power to detect a difference in the supposed incidence of biliary complications of 15% (30% in the T-tube drainage group versus 15% in the Roux-en-Y HJ group). Given an estimated withdrawal rate of 10%, the minimum required sample size would be 204 patients. We plan to enrol a total of 210 patients (105 per group).

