### Statistical analysis

The two-sided null hypothesis for the primary outcome measure states that both study interventions lead to a similar rate of stone recurrence; the alternative hypothesis is that one intervention will perform better than the other. The continuous variables will be recorded as the mean ± SD (for normally distributed variables) or medians and interquartile ranges (for skewed parameters) and will be statistically analysed with Student’s *t* test and the non-parametric Mann-Whitney *U* test, respectively.

Categorical data will be presented as frequencies and group percentages and compared with Fisher’s exact test. Graded data, including age, quality of life and Clavien-Dindo classification, will be compared with the Wilcoxon signed-rank test.

The odds ratio for having biliary complications will be determined with a logistic regression model. The homogeneity of the two groups will be described by comparing the demographic data and the baseline values.

All analyses will be performed on an intention-to-treat (ITT) basis. Statistical Package for the Social Sciences (SPSS) 10.0 (SPSS Inc., Chicago, IL, USA) will be used for statistical analysis. Statistical significance will be defined as *P* < 0.05.

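### The 93 per group matches a one-sided 5% calculation; the planned two-sided 5% test has about 64–70% power at that size, not 80%

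*Protocol article*

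**What the plan says.** In the Protocol article, the section Number of patients needed describes the basis: "The sample size is based on a two-sided *t* test for differences with respect to the primary parameter and the primary analysis". It assumes a 30% incidence of biliary complications with T-tube drainage, from the centre's own retrospective series, and 15% with Roux-en-Y hepaticojejunostomy. The result is "The calculated sample size was 186 (93 per group), with 80% statistical power to detect a difference". On losses it says: "Given an estimated withdrawal rate of 10%, the minimum required sample size would be 204 patients". Planned enrolment is 210, or 105 per group.

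The Statistical analysis section refers to "The two-sided null hypothesis for the primary outcome measure" and adds "Statistical significance will be defined as *P* < 0.05". Categorical variables are to be "compared with Fisher’s exact test". The same section also plans a logistic regression for the odds ratio of biliary complications. A one-sided test or a 10% significance level is mentioned nowhere.

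**The concern.** For 30% versus 15% at two-sided 5% and 80% power, any usual formula gives roughly 120 per group. A figure of 93 is too small by about a fifth to a quarter, more than rounding or choice of formula can explain.

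Power is a stated property of the design, and readers will use it to interpret the result. If the trial finds no significant difference, the article invites the reading that a halving of complications had only a 20% chance of being missed. If the true chance is nearer one in three, a null result would be over-read as evidence that the two operations are equivalent.

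**Working it through.** **Inputs.** Two-sided test, 80% power, 30% versus 15%, 93 per group, 10% withdrawal and 210 enrolled come from Number of patients needed. The 5% level comes from Statistical analysis; the sample size paragraph gives no alpha. The 1:1 allocation comes from Randomization and blinding.

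**Reproducing the plan's figure.** The unpooled formula is n = (z_α + z_β)² × [p₁(1−p₁) + p₂(1−p₂)] / (p₁−p₂)². The variance term is 0.21 + 0.1275 = 0.3375, and 0.3375 / 0.0225 = 15.

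- One-sided 5%: (1.645 + 0.842)² × 15 = 92.7, so **93**. This is the plan's number exactly.
- Two-sided 5%: (1.960 + 0.842)² × 15 = 117.7, so **118**.

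**Could another formula give 93 two-sided?** No:

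| Formula | Two-sided 5%, n per group | One-sided 5%, n per group |
|---|---|---|
| Unpooled variance | 118 | 93 |
| Arcsine | 119 | 94 |
| Pooled variance | 121 | 95 |
| t test on means, SD = √(0.225 × 0.775) | 122 | 96 |
| Pooled with continuity correction | 134 | 108 |

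The t test label does not explain the figure either, since that formula gives 122.

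**Power actually available.** With the unpooled normal approximation at 93 per group, the standard error is √(0.3375/93) = 0.0602 and 0.15/0.0602 = 2.490.

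- Two-sided: Φ(2.490 − 1.960) = Φ(0.530) = 70.2%.
- One-sided: Φ(2.490 − 1.645) = Φ(0.845) = 80%, the advertised value.

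Exact power, by summing over all binomial outcomes for 30% versus 15% at two-sided 5%:

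| Analysed per group | Chi-square (uncorrected) | Fisher's exact |
|---|---|---|
| 93 | 69.7% | 63.7% |
| 94 | 70.2% | 64.3% |
| 95 | 70.7% | 64.9% |
| 105 (no losses) | 75.0% | 69.8% |

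The rows for 94 and 95 bracket the plan's own expectation of 210 × 0.9 = 189 evaluable patients. Fisher's test first reaches 80% at 131 per group (80.1%).

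**Difference detectable with about 80% power, against 30% in the T-tube group.**

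- 94 per group, chi-square: about 16.5 points (30% versus 13.5%, power 79.5%).
- 94 per group, Fisher: 74.5% at that difference; it needs about 17.5 points (30% versus 12.5%, power 80.6%).
- 105 per group, chi-square: about 16 points (30% versus 14%, power 81.0%).
- 105 per group, Fisher: about 16.5 points (30% versus 13.5%, power 79.6%).

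**Withdrawal allowance.** To keep 186 after 10% loss, 186 / 0.9 = 206.7, so 207, or 208 in two equal groups. The stated 204 matches 186 × 1.1 = 204.6 with the decimal dropped. It would leave 204 × 0.9 = 183.6, short of 186.

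**The case against.** The strongest counter-argument is that the 64–70% range uses the smallest sample. The plan enrols 105 per group and specifies intention-to-treat analysis, so 70–75% may be the fairer range, with a 25–30% chance of missing the effect. This is a legitimate scenario, but it still falls short of 80%. The extra patients are the allowance for withdrawals, and the Withdrawal section says that data from patients who withdraw will not be used. About 189 evaluable patients is therefore the plan's own expectation.

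Second, that a one-sided 5% level was used is an inference from the exact match; two-sided 10% gives the same number. That stands, but either explanation contradicts the stated two-sided 5% test.

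Third, Fisher's test is assigned to categorical data generally, and a logistic model is also named for biliary complications. The 64% and the 131 per group therefore apply only if Fisher's test is the primary comparison. With the uncorrected chi-square test the shortfall is smaller but remains.

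Fourth, the withdrawal slip and the t test label have little consequence: 210 exceeds 208, and the label did not produce the 93. Both are minor corrections.

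Finally, the Trial status section says the study will run until power is sufficient. No re-estimation rule accompanies that statement, so it does not repair the calculation.

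**Conclusion.** The concern holds; the sample size statement is wrong as written. Under the plan's own inputs, 80% power needs 118–122 analysed patients per group by the standard uncorrected formulas, or 131 with Fisher's test, against 93 calculated and 105 enrolled. Power with the uncorrected chi-square test or Fisher's test respectively is 70% or 64% at 93 per group, 70–71% or 64–65% with 10% losses from 210, and 75% or 70% with none. No reading of the two-sided 5% plan gives 80%.

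This rests on taking alpha from the Statistical analysis section, on the assumed 30% and 15% being correct, and on a simple comparison of two proportions. The named t test and the 204 are secondary errors that do not affect the conclusion.

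**What to change.** Keep 210 patients and rewrite the paragraph:

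- Replace the t test with a comparison of two proportions, two-sided alpha 0.05, and name the primary test.
- Replace 80% with about 70% power for 189 evaluable patients and about 75% if all 210 are analysed. If Fisher's test is primary, give 64–65% and 70%.
- Correct 204 to 207 (208 balanced) where the allowance for 186 evaluable patients is described.
- State what 210 patients can detect with about 80% power: with 10% losses, about 16.5 points (chi-square) or 17.5 points (Fisher); with none, about 16 or 16.5 points.
- Bring the Trial status sentence about continuing until power is sufficient into line with the restated figures.

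This is a wording change that needs no extra patients; its only cost is a less favourable stated power. If the sponsor wants a true 80%, that is a separate decision. The pooled figure of 121 per group gives 242 / 0.9 = 268.9, so about 270 enrolled. Fisher's test gives 262 / 0.9 = 291.1, so 292 in two equal groups.

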### Eligibility criteria

#### Inclusion criteria

The following are the inclusion criteria:
Aged between 18 and 70 yearsDiagnosed with HL with SOL during the operationUnderwent foci removal, stone extraction without residue and stricture correction during the operationProvided written informed consentWas willing to complete a 3-year follow-up.

#### Exclusion criteria

The following are the exclusion criteria:
Participation in concurrent intervention trials that would interfere with the outcomes of this studyAssociated tumourComplete loss of function or normal sphincter of Oddi (SO)Previous choledochojejunostomyIntraoperative stone residualLack of compliance

### Withdrawal

An informed consent form, which describes the detailed study procedures and illustrates the potential benefits and risks, will be provided to all participants so that they can decide whether to volunteer. All the participants are freely informed to participate in the study and can withdraw from the trial at their own request at any time. If the patient withdraws, the information will not be used in this study. However, the research team can still record the outcome data in clinical report forms.

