### Randomization and blinding

To achieve comparable groups of known and unknown risk factors, randomization will be performed. Patients meeting the eligibility criteria will be randomly assigned (1:1) to the T-tube drainage arm or Roux-en-Y HJ arm by computer-generated allocation based on the envelope method and the hierarchical block randomization method. The envelopes will be opened after common bile duct exploration.

Blinding of the surgeons and patients is not feasible due to the obviously different characteristics of the two types of biliary drainage. However, the statisticians will be blinded to the treatment allocation during data collection and analysis.

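### The withdrawal rule leaves withdrawn patients' data unused, which conflicts with the intention-to-treat rule and can bias the primary comparison

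*Protocol article*

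**What the plan says.** The Withdrawal section says that participants "can withdraw from the trial at their own request at any time". It continues: "If the patient withdraws, the information will not be used in this study". The sentence after that reads: "However, the research team can still record the outcome data in clinical report forms". It does not say whether outcomes recorded in this way enter any analysis.

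The Statistical analysis section says: "All analyses will be performed on an intention-to-treat (ITT) basis". It makes no exception for patients who withdraw.

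Three other parts of the article matter here:

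- Number of patients needed allows for 10% withdrawal and plans 210 patients, 105 per group. The target is "30% in the T-tube drainage group versus 15% in the Roux-en-Y HJ group".
- Randomization and blinding says: "Blinding of the surgeons and patients is not feasible due to the obviously different characteristics of the two types of biliary drainage". Allocation is revealed during surgery: "The envelopes will be opened after common bile duct exploration".
- The primary endpoint is the incidence of biliary complications over 3 years. The Fig. 2 caption lists visits at 3 and 6 months and at 1, 2 and 3 years.

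**The concern.** Intention-to-treat means that every randomised patient is analysed in the assigned arm. A rule that leaves a withdrawn patient's information out of the study removes that patient from the comparison after randomisation. The two statements cannot both be applied to the same patient.

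The rule also loses information that is not missing. Suppose a stone recurrence is found at the 1-year visit and the patient withdraws before the 2-year visit. The primary event is already known, yet under the rule as written it is not used.

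What is at stake is the randomised comparison itself. Patients know which drainage they received, the two procedures differ visibly, and follow-up lasts at least 3 years. Patients may leave because of their allocation or because of an early complication. If leaving is related to outcome, and this differs by arm, excluding the leavers shifts the observed difference. Blinding the statisticians does not protect against this, because the selection happens before the data reach them.

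**Working it through.** **1. The texts side by side.** The withdrawal rule says that the information is not used. The analysis rule says that all analyses are by intention-to-treat. The recording sentence allows collection and is silent on analysis. Nothing else in the article links the three. A separate analysis plan could add methods for missing outcomes, but it could not make both rules true for a patient who withdraws.

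**2. The plan's own allowance.** From Number of patients needed: 186 × 1.10 = 204.6, stated as 204. (Dividing instead, 186/0.90 = 206.7, or 207.) The planned 210 covers both. Ten per cent of 210 is 21 patients. Nothing below depends on how 186 was derived.

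**3. Effect of exclusion when the arms are truly equal.** Let p be an arm's true 3-year risk, w the fraction withdrawing and e the 3-year event risk among withdrawers. The risk seen after exclusion is

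(p − w × e) / (1 − w)

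The article gives no values for e or for the split by arm, so the following are assumptions: p = 25% in both arms, and w = 5% in one arm and 15% in the other. With 105 per arm this is 5.25 + 15.75 = 21 patients, which matches the allowance.

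| e | Arm with w = 5% | Arm with w = 15% | Spurious difference |
|---|---|---|---|
| 25% (unrelated to outcome) | (0.25 − 0.0125)/0.95 = 25.0% | (0.25 − 0.0375)/0.85 = 25.0% | 0 |
| 50% | (0.25 − 0.025)/0.95 = 23.7% | (0.25 − 0.075)/0.85 = 20.6% | 3.1 points |
| 60% | (0.25 − 0.03)/0.95 = 23.2% | (0.25 − 0.09)/0.85 = 18.8% | 4.3 points |

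Against the 15-point target, 3.1/15 = 21% and 4.3/15 = 29%. The arm that loses more high-risk patients looks better.

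**4. Direction under the planned effect.** Take true risks of 30% (T-tube) and 15% (Roux-en-Y hepaticojejunostomy, HJ), 105 per arm and 21 withdrawals in total. The splits and risks are again assumed. With m withdrawals, the observed risk is (105p − m × e)/(105 − m).

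- Withdrawal unrelated to outcome: the difference stays at 15.0 points.
- 16 T-tube withdrawers at 60% risk and 5 HJ withdrawers at 15%: (31.5 − 9.6)/89 = 24.6% and (15.75 − 0.75)/100 = 15.0%, a difference of 9.6 points.
- 5 T-tube withdrawers at 30% and 16 HJ withdrawers at 50%: (31.5 − 1.5)/100 = 30.0% and (15.75 − 8)/89 = 8.7%, a difference of 21.3 points.

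**5. False-positive rate.** Take equal true risks of 22.5%, with 5 T-tube withdrawers at 22.5% and 16 HJ withdrawers at 50%. The T-tube arm shows 22.5% and the HJ arm (23.625 − 8)/89 = 17.6%, a spurious 4.9 points. A normal approximation with 100 and 89 patients analysed gives a rejection probability of about 13% instead of 5%. Swapping the arms reverses the sign.

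**The case against.** The best defence is that the wording is loose rather than wrong. The article does not define the information concerned, and leaving data unused is not the same as destroying them. The recording sentence opens as a contrast and might be meant to rescue outcomes after withdrawal, which would serve intention-to-treat. This stands as far as it shows an ambiguity. It does not remove the conflict, because permission to record is not a statement that the data are analysed.

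It is also fair that the splits and withdrawers' risks above are assumed, that bias may be absent, and that the consent form, which is not shown, governs what may be kept after withdrawal.

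Some stronger readings are tempting but not supported:

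- A reader might infer that the exclusion criterion on poor compliance also removes patients after allocation. It is an eligibility criterion, and Randomization and blinding says that only eligible patients are randomised. Nothing applies it later.
- A reader might take 21 as the number who will be affected. It is a planning allowance, and it may include loss to follow-up, which the withdrawal rule does not address.
- A reader might conclude that the planned binary analysis cannot handle partial follow-up and must give way to Kaplan-Meier estimation. A binary analysis can count events before withdrawal, and unknown outcomes can be imputed or bounded. Censoring at last contact would itself assume that withdrawal is unrelated to outcome.

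**Conclusion.** The point holds. The withdrawal rule and the intention-to-treat rule conflict in the text of the article, and nothing shown reconciles them. Followed literally, the withdrawal rule drops randomised patients and any primary events already observed in them.

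The bias is possible, not certain, and its direction is unknown. It is zero if withdrawers carry the same risk as the others in their arm. It is about 3 to 4 points with 5% versus 15% withdrawal, a 50 to 60% risk in withdrawers and a true risk of 25% in both arms. Other assumed splits of 21 withdrawals move a true 15-point difference to between 9.6 and 21.3 points. Within the planned allowance, at most about 21 of 210 patients are concerned. The inconsistency itself rests on none of these assumptions.

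**What to change.** Replace the sentence on unused information with wording such as:

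> Data collected up to withdrawal are kept and analysed in the arm assigned at randomisation; outcome follow-up continues if the patient agrees.

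Then:

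- Align the consent form with this wording. Enrolment began on 1 February 2020, so if patients already enrolled were promised otherwise, the ethics committee needs to consider how their data may be used.
- Keep the planned binary analysis, and state that any biliary complication before withdrawal counts as an event.
- Add best-case and worst-case sensitivity analyses for patients whose 3-year status is unknown: all of them events in one arm and event-free in the other, then the reverse.

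The cost is a change of wording, a possible ethics submission and a little extra analysis. The bounds may be wide. With unknown status in 10% of each arm, the two extremes lie 10 + 10 = 20 percentage points apart, more than the 15-point target. That is a reason to continue outcome follow-up where patients agree, so that few outcomes remain unknown.
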